# Impact of mobile health technologies on human papillomavirus vaccination uptake among mothers of unvaccinated girls aged 9–14 years in Lagos, Nigeria (mHealth-HPVac): Study protocol of a randomised controlled trial

**DOI:** 10.21203/rs.3.rs-4541493/v1

**Published:** 2024-06-27

**Keywords:** Cervical cancer, Lagos, mHealth-Cervix, NHIS, Nigeria, Pap test

## Abstract

**Background::**

Despite the availability of effective vaccines, human papillomavirus (HPV) vaccine uptake remains low in most resource-limited settings including Nigeria. Mobile health technology (mHealth) may empower patients to control their health, reduce inequalities, and improve the uptake of HPV vaccination.

**Aim::**

The *“mHealth-HPVac”* study will assess the effects of mHealth using short text messages on the uptake of HPV vaccination among mothers of unvaccinated girls aged 9–14 years and also determine the factors influencing the uptake of HPV vaccination among these mothers.

**Methods::**

This protocol highlights a randomised controlled trial involving women aged 25–65 years who will be enrolled on attendance for routine care at the General Outpatient clinics of Lagos University Teaching Hospital, Lagos, Nigeria between July and December 2024. At baseline, n=224 women will be randomised to either a short text message or usual care (control) arm. The primary outcome is vaccination of the participant’s school-age girl(s) at any time during the 6 months of follow-up. The associations between any two groups of continuous variables will be tested using the independent sample t-test (normal distribution) or the Mann-Whitney U test (skewed data) and that of two groups of categorical variables with Chi-square (*X2*) or Fisher’s exact test where appropriate. Using the multivariable binary logistic regression model, we will examine the effects of all relevant sociodemographic and clinical variables on HPV vaccination uptake among mothers of unvaccinated but vaccine-eligible school-age girls. Statistical significance will be defined as A *P*<0.05.

**Discussion::**

The mHealth-Cervix study will evaluate the impact of mobile technologies on HPV vaccination uptake among mothers of unvaccinated but vaccine-eligible school-age girls in Lagos, Nigeria as a way of contributing to the reduction in the wide disparities in cervical cancer incidence through primary prevention facilitated using health promotion to improve HPV vaccination uptake.

**Registration::**

PACTR202406727470443 (6^th^ June 2024).

## Introduction

In 2020, there were an estimated 604,000 new cases of cervical cancer and 342,000 deaths from cervical cancer, with 70% of these deaths occurring in developing countries [1]. Persistent infection of the cervix with certain high-risk genital human papillomavirus (HPV) is a necessary cause of cervical cancer [2, 3]. One of the most effective strategies for cervical cancer prevention is vaccination against HPV infection among young and adolescent girls before the start of sexual activity [2, 4].

Administering HPV vaccines in low and middle-income countries is essential for achieving the global action plan aimed at bridging the cervical cancer gap [5]. HPV vaccine rollout to girls aged 9–14 years as recommended by the World Health Organization (WHO) [6] is projected to have a greater and faster direct impact and herd effects on the population’s immunity [7]. There are four vaccines against HPV infections[8, 9] and only two of these (quadrivalent Gardasil and bivalent Cervarix) are currently approved for use by the Nigerian Federal Ministry of Health [10, 11]. In October 2023, Nigeria embarked on new routine HPV vaccine roll-out campaigns to reach about 7.7 million girls [12]. Under this new immunization protocol, girls aged 9 to 14 years will receive a single dose of the vaccine [12], which is highly effective at preventing infection of HPV types 16 and 18 that are known to cause at least 70 per cent of cervical cancers [2].

Despite the availability of effective vaccines, HPV vaccine uptake remains low in most resource-limited settings including Nigeria [5, 12, 13]. The utilization of mobile technologies has increased significantly in recent years [14] with increased opportunities for mobile health technologies (mHealth) development [15]. Mobile health technology (mHealth) may empower patients to control their health, reduce inequalities [16], and improve the uptake of health interventions such as HPV vaccination. There are only a few reported studies in Sub-Saharan Africa that examined the use of mHealth in cancer prevention [16] but there are currently none that have investigated the impact of this intervention on the uptake of HPV vaccination among mothers of eligible unvaccinated vaccine-eligible school-age girls.

The primary objective of this proposed study *“mHealth-HPVac”*, therefore, is to assess the effects of mHealth using short text messages on the uptake of HPV vaccination among mothers of unvaccinated girls 9–14 years while the secondary objective is to determine the factors affecting the uptake of HPV vaccination among mothers of unvaccinated girls aged 9–14 years under usual conditions. This is innovative because the introduction of mHealth, now regarded as one of the most promising investments for health in developing countries [17], is a novel concept in the paradigm shift for disease prevention which can contribute to improving cervical cancer control in the resource-limited settings of sub-Saharan Africa (SSA). Thus, the study will generate the first real-world evidence in SSA on the efficacy of mobile technologies on HPV vaccination uptake among eligible school-age daughters of participating mothers in Nigeria.

## Methodology

### Study design and setting

*“mHealth-HPVac”* is a randomised parallel arm controlled trial of mothers of unvaccinated girls aged 9–14 years who attend routine care at the General Outpatient (GOP) clinics of the Lagos University Teaching Hospital (LUTH), Nigeria between June and October 2024. LUTH is the foremost healthcare institution in Lagos and serves as a referral centre for other government-owned and private hospitals in Lagos and its neighbouring states. The hospital provides various care including integrated gynecologic oncology prevention services such as Pap smearing, human papillomavirus testing, colposcopy and pathologic services, including cytology and histology [18]. The GOP clinic of the hospital is opened on each day of the week with attendees being mainly enrollees of the National Health Insurance Scheme.

### Study population

Eligible participants are mothers of unvaccinated girls aged 9–14 years; who express willingness to vaccinate their children; own and use a personal cellphone; free from any mental or physical disabilities that inhibit them from understanding the implications of the study and not considering relocating from their current residence within the next year. The exclusion criteria include refusal of consent or withdrawal of consent during the study.

### Study endpoints and sample size calculation

The *primary endpoint* is the prevalence of single-dose HPV vaccination uptake after 6 months and the *secondary endpoints* are predictors of HPV vaccination uptake after 6 months of enrolment among participating mothers of young or adolescent girls aged 9–14 years. Participants will be tracked via medical record review as well as through phone calls in the 7th month after their enrolment to collect data on their HPV vaccination uptake. With pooled HPV vaccine uptake prevalence of 28.5% for a usual care condition derived from the systematic review by Asgedom et al [19] and an expected attrition rate of 20%, a sample size [20] of n=123 women is expected to provide 80% power to establish a 30% proportional difference in HPV vaccination uptake between mHealth intervention and usual care condition.

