## Discussion

Cervical cancer, the most common HPV-associated malignancy, is a major public health disease in Nigeria. However, despite the availability of effective vaccines, HPV vaccine uptake remains low in most resource-limited settings including Nigeria [5, 12, 13]. The utilization of mobile technologies has increased significantly in recent years[14] with increased opportunities for mobile health technologies (mHealth) development [15]. Mobile health technology (mHealth) may empower patients to control their health, reduce inequalities [16], and improve the uptake of health interventions such as HPV vaccination. Currently, no study has investigated the use of mobile technologies to enhance HPV vaccination uptake. This protocol, therefore, describes a randomised controlled trial of mHealth technologies using text messages to improve HPV vaccination uptake by evaluating the impact of mobile technologies on HPV vaccination uptake among mothers of unvaccinated girls 9–14 years in Lagos, Nigeria and also determine the factors that affect this vaccination uptake as a means of reducing the disparities in the incidence of cervical cancer through primary prevention facilitated using health promotion to improve HPV vaccination uptake. We have powered the study to detect the primary outcome to show that mHealth can improve HPV vaccine uptake in mothers of unvaccinated girls aged 9–14 years. We believe that if found to be effective, the mHealth intervention strategy may become an important tool for reducing the cervical cancer burden, and its associated morbidity and mortality. This approach could also be utilized for health promotion and prevention efforts targeting other significant diseases in the future. However, a limitation of this trial is that we have not specifically powered to detect the predictors of HPV vaccination uptake in these mothers (although this is a planned secondary outcome). The trial would need to be significantly larger to detect these influencing factors. However, the study will generate preliminary data for hypothesis testing in a future robust and carefully designed prospective cohort study.

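### The abstract randomises 224 women but the sample-size section justifies 123, and the target effect is worded so that it can mean 30 percentage points or a 30% relative rise

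*Protocol article*

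**What the plan says.** The Methods paragraph of the abstract states: "At baseline, n=224 women will be randomised to either a short text message or usual care (control) arm". It gives no effect size, power or attrition for that number.

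The section on study endpoints and sample size calculation gives a different number. It starts from a usual-care rate, "With pooled HPV vaccine uptake prevalence of 28.5% for a usual care condition", allows for 20% attrition, and concludes that "a sample size [20] of n=123 women is expected to provide 80% power to establish a 30% proportional difference in HPV vaccination uptake". It does not say whether 123 is the whole trial or one arm. It gives no uptake rate for the intervention arm.

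The section on data management and statistical analysis sets a two-sided 5% significance level and a Pearson chi-square or Fisher's exact test. The Discussion says: "We have powered the study to detect the primary outcome". Under Study Status, recruitment had not begun when the article was submitted.

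**The concern.** Both numbers stand in current text, and nothing in the article connects them. The recruitment target is therefore undefined, and a later shortfall or over-recruitment could not be judged against it.

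The effect is just as unclear. The plan describes "a 30% proportional difference in HPV vaccination uptake between mHealth intervention and usual care condition". Starting from 28.5%, this can mean adding 30 percentage points (to 58.5%) or multiplying by 1.30 (to 37.05%). The first roughly doubles uptake and the second is a modest gain. The sample sizes they need differ about tenfold, so a reader cannot tell what the trial is built to detect.

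**Working it through.** **Inputs.** Control rate p1 = 28.5%, power 80% and attrition 20% (sample-size section); two-sided alpha 5% (statistical analysis section). Allocation of 1:1 is my assumption; the article names two arms but no ratio.

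**Formula per arm.** With d = p2 − p1, p̄ the mean of the two rates, and z values 1.960 and 0.842:

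n = [1.960·√(2p̄(1−p̄)) + 0.842·√(p1(1−p1) + p2(1−p2))]² / d²

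The continuity-corrected version is n′ = (n/4)·[1 + √(1 + 4/(n·d))]². Attrition is handled by dividing by 0.8.

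**Step 1: do the two totals convert?** 2 × 123 = 246, not 224. 123/0.8 = 153.75, so 154, not 224; and attrition is already inside the 123.

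**Step 2: reproduce 123 (30 points, p2 = 58.5%).** p̄ = 0.435 and n = 3.750/0.09 = 41.7. With continuity correction n′ = 48.1, so 49 per arm and 98 in total. 98/0.8 = 122.5, rounded up to 123. This matches exactly if 123 is the total. Without the correction the result is 42 per arm, 84 in total, 105 after inflation.

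**Step 3: the relative reading (p2 = 1.30 × 28.5% = 37.05%).** d = 0.0855, p̄ = 0.32775, n = 3.450/0.00731 = 471.9, so 472 per arm. 472/0.8 = 590 per arm, or 1,180 randomised.

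**Step 4: power after 20% attrition** (uncorrected test). 123 randomised leaves 49.2 per arm; 224 leaves 89.6 per arm.

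| True uptake, control vs intervention | 123 in total | 224 in total |
|---|---|---|
| 28.5% vs 58.5% (30 points) | 86% | 99% |
| 28.5% vs 48.5% (20 points) | 53% | 79% |
| 28.5% vs 37.05% (30% relative) | 14% | 23% |

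For 30 points, the continuity-corrected figures are about 81% and 98%. If 123 were per arm (246 in total), power for the relative rise would still be only about 25%.

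**Step 5: what could 224 rest on?** Assuming 80% power and 20% attrition, several designs land on or near it:

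- 20 points with the unpooled, uncorrected formula: 89.0 per arm, /0.8 gives 112 per arm, 224 in total. The pooled formula gives 92 per arm and 230 in total.
- 21.5 points (28.5% vs 50%) with continuity correction: 89 per arm, 112 after inflation, 224 in total.
- A 30% relative cut in non-uptake (71.5% to 50.05%) with continuity correction: 90 per arm, 180/0.8 = 225.

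So 224 corresponds to roughly 20 to 21.5 points, depending on the formula, and the document does not identify which was used, if any.

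**Step 6: is the decoding of 123 unique?** Not quite. A 20-point rise with the unpooled, continuity-corrected formula needs 98.7 per arm, and 98.7/0.8 = 123.4. So 123 could also be approximately a per-arm figure for a different effect. The missing label matters.

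**The case against.** The best defence is that the calculation behind 123 is sound. Read as a difference between two proportions of 30 points, it reproduces to the last woman with a standard formula, which is good evidence that this is what was computed. On that reading 123 gives the stated 80% power and 224 gives far more. This stands, and it rules out two stronger claims that a reader might infer.

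The first is that neither number gives 80% power, so that the Discussion's powering statement is false. That holds only on the relative reading, which the exact match makes the less likely one. On the 30-point reading both numbers exceed 80%.

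The second is that 123 and 224 rest on different effect sizes. The article states no effect for 224. The tidy pairing of 30 points with 123 and 20 points with 224 needs the continuity correction for one and an unpooled, uncorrected formula for the other. With a single formula the pair does not appear: continuity-corrected, 20 points needs about 255; unpooled and uncorrected, 30 points needs about 98. The 224 could equally be a leftover figure or a deliberately larger target.

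The defence does not reach the conflict between the two totals, the missing label on 123, or wording that a reader can resolve only by reverse calculation. Nor does condensing a protocol into an article explain why it states two different sizes.

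**Conclusion.** The sample size is wrong as written: 224 and 123 cannot both be the trial's size, and the text offers no way to choose. The effect is ambiguous between two readings with very different consequences. At 30 points, 123 in total is right and 224 has about 99% power without a stated reason for the excess. At a 30% relative rise, about 1,180 women are needed and power is about 14% with 123 and 23% with 224. The choice of total also matters for effects in between: for 20 points, 53% against 79%.

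These figures assume 1:1 allocation, a 28.5% control rate and 20% loss in each arm. The relative-reading figures are conditional on a reading that the reproduced 123 makes less likely. The 20 to 21.5 points attached to 224 are a back-calculation, not a design assumption found in the document.

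**What to change.** State one total in the abstract and in the sample-size section, with the per-arm count, the control and intervention percentages, the formula (with or without continuity correction) and the attrition inflation. Replace the percentage-difference wording with the two arm percentages.

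- If 123 is the target and the sponsor confirms the basis: 28.5% versus 58.5%, 123 women in total, continuity-corrected, inflated for 20% attrition.
- If 224 is the target: state the effect it detects with 80% power after 20% attrition (about 20 points), once the sponsor has confirmed what the number was based on. The back-calculated rate should not be written in as a design assumption without that confirmation.

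The powering statement in the Discussion should then refer to the effect so stated.

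The cost is wording only, with no extra patients, and it can be done before enrolment opens. The stated detectable effect may look less favourable. If the sponsor says that a 30% relative rise was meant, neither total supports 80% power, and the stated target effect or the size would have to change.

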### Participants’ enrolment and data collection

A 20–30-minute health talk on cervical cancer prevention including HPV vaccination is given by the clinic midwives as part of usual care to all women in the clinics after which the investigators or research assistants will screen and identify eligible women for the study [Figure 1]. The women will then be invited to give consent for participation upon explanation of the purpose and procedures of the study. Once consent is obtained, an electronic interviewer-administered questionnaire created on the REDCap database will be applied to each participant to obtain baseline information on sociodemographic variables, cellphone use and distance of participants’ residence from the clinics (measured in kilometres using Google map).

### Randomization and allocation concealment

Once enrolled, eligible women will be randomised to either a text message (intervention) arm or a usual care (control) arm using a computer-generated random sequence generated by an independent statistician.

*Intervention (mHealth) arm* – MultiTexter Bulk short message service (SMS) will be used as the platform to deliver the mHealth messages given its reliability and low cost. Participants will be sent messages containing information on cervical cancer and are then encouraged to take their daughters aged 9–14 years for HPV vaccination. Text messages will be delivered monthly for 6 months after enrollment.*Usual care (control) arm* – Participants in this study arm will only receive the usual health education talk at enrolment. They will receive no additional follow-up text messages.

Group allocations will be concealed from the investigators and trial statistician using sealed opaque envelopes that are sequentially numbered. The envelopes will be prepared in advance of the trial and will only be opened sequentially at the time of participants’ enrollment, ensuring that the treatment allocation remains concealed until the point of assignment. Given that no safety concerns are expected, we do not anticipate the need for unblinding during the study.

### Data management and statistical analysis

Data collection will occur prospectively with data entry and checking taking place continuously. Queries will be followed vigorously to ensure clarification without delay. Participants’ enrolment will be facilitated by providing clear, concise, and understandable information about the study’s purpose, procedures, benefits, and risks using compelling language and visuals to make the study interesting and engaging. Each participating woman will be offered free cervical cancer screening if desired and will receive an estimated $2.50 credit charge on their cellphones as a token to enable the investigators to keep their phone numbers for as long as the intervention lasts. We also anticipate some participants’ fatigue and drop-outs during the study’s follow-up period. We will, therefore, mitigate these by training and providing support to the study team on study protocols, including retention techniques such as good communication skills, cultural competence, and specialized knowledge of the target population. The intention-to-treat principle will be used in the final analysis. Data will be analyzed using SPSS version 29.0 for Windows. The participants’ characteristics, by intervention arm, will be presented as mean (standard deviation), median (25th–75th centile), and frequency (%) depending on type and distribution. The significance level is *P*<0.05 and all hypothesis testing will be two-sided. We will test the associations between the intervention and HPV vaccination uptake using Pearson’s Chi-square (χ2) or Fisher’s exact test where appropriate. Using multinomial logistic regression analysis, we will adjust for the effects of all possible covariates in this association. In a subgroup analysis of women in the usual care arm, a multivariable binary logistic regression model will be developed using a backward stepwise selection approach to identify factors such as participant’s age, socioeconomic class, parity, marital status, number of GOP clinic attendance, the distance of residence from the clinics, the functionality of cellphones, adolescent girl’s age and school level and other relevant demographic and clinical variables as that are independently associated with HPV vaccination uptake after 6-months of follow-up. Variables associated with vaccination uptake (*P*<0.10) in the bivariable analyses will be included in the pool of variables for the backward stepwise regression model. An Akaike’s Information Criterion will be generated constantly and the last model step with the smallest AIC is then selected as the best-fit model. Associations in the final model are regarded as significant if *P*<0.05.

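### The predictors analysis screens and stepwise-selects factors on about 14 to 26 usual-care events, so intervals for retained factors will under-cover and odds ratios of detected predictors will be exaggerated; the stated power limitation does not cover this.

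*Protocol article*

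**What the plan says.** Predictors of uptake are the secondary objective (end of the Introduction) and the secondary endpoints (Study endpoints and sample size calculation). Data management and statistical analysis sets out the method in full:

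- **Analysis set:** "In a subgroup analysis of women in the usual care arm".
- **Model building:** "a multivariable binary logistic regression model will be developed using a backward stepwise selection approach to identify factors".
- **Screen:** variables with P<0.10 "in the bivariable analyses will be included in the pool of variables for the backward stepwise regression model".
- **Final model:** the step with the smallest AIC. Associations in it are significant if P<0.05, and the factors are described as independently associated with uptake.
- **Candidates:** nine are named (mother's age, socioeconomic class, parity, marital status, clinic attendances, distance, cellphone functionality, girl's age, school level). An unspecified set of other relevant demographic and clinical variables is added.

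The Discussion concedes that "a limitation of this trial is that we have not specifically powered to detect the predictors of HPV vaccination uptake", that a significantly larger trial would be needed, and that the results are preliminary data for a future cohort study. The Abstract describes a multivariable logistic model for uptake without restricting it to one arm.

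**The concern.** The same small data set is used three times: to decide which variables enter, to decide which stay, and to judge their significance. The final P-values and intervals are then computed as if the model had been fixed in advance. A factor survives partly because its estimate happened to be large in this sample, so the surviving estimates are biased away from the null and their intervals are misplaced. The fewer the events, the larger this effect.

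At stake is the credibility of the secondary endpoint. Factors called independently associated with uptake, with odds ratios that are too large, would be the starting point for the cohort study that the Discussion envisages. The protocol states this method outright, so the point is not about detail left to a statistical analysis plan.

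**Working it through.** **Inputs.** All but the allocation ratio come from the protocol.

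- Usual-care uptake: "With pooled HPV vaccine uptake prevalence of 28.5% for a usual care condition" (Study endpoints and sample size calculation).
- Attrition: "an expected attrition rate of 20" per cent (same section).
- Sample size: "of n=123 women is expected to provide 80% power" (same section), but 224 in the Abstract. Both are carried through.
- Effect: "a 30% proportional difference in HPV vaccination uptake between mHealth intervention and usual care condition" (same section).
- Two-sided 5% level (Data management and statistical analysis).
- Allocation ratio: not stated; 1:1 is assumed.

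**Is 123 a two-arm total?** Read the effect as 30 percentage points, 28.5% against 58.5%, with mean 0.435.

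- Uncorrected n per arm = [1.96 × √(2 × 0.435 × 0.565) + 0.8416 × √(0.285 × 0.715 + 0.585 × 0.415)]² / 0.30² = 41.7.
- With continuity correction: (41.7/4) × [1 + √(1 + 4/(41.7 × 0.30))]² = 48.1, rounded up to 49 per arm, 98 in total.
- With attrition: 98/0.80 = 122.5, rounded up to 123.

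The stated figure is reproduced as a total for both arms.

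**Events in the usual-care arm** = (N/2) × 0.80 × 0.285.

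| Enrolled | Retained in arm | Vaccinated | Per named candidate (÷ 9) |
|---|---|---|---|
| 123 | 49.2 | 14.0 | 1.6 |
| 224 | 89.6 | 25.5 | 2.8 |

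With no attrition the events are 61.5 × 0.285 = 17.5 and 112 × 0.285 = 31.9, or 1.9 and 3.5 per candidate. Dummy terms for multi-category factors and the unnamed extras lower all these ratios.

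**False findings when no candidate matters.** The stated procedure (P<0.10 screen, backward elimination on AIC, final P<0.05) was simulated with independent normal candidates, 1,500 runs per setting. In repeated sets of runs, at least one factor was declared significant in:

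- about 31% of trials (n=49) or 34% to 35% (n=90) with 9 candidates;
- about 45% (n=49) or 48% to 51% (n=90) with 15 candidates.

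The right comparator is the chance of at least one hit among that many independent 5% tests: 1 − 0.95⁹ = 37% and 1 − 0.95¹⁵ = 54%. The simulated figures are no higher than these. The mean number of false factors was 0.36 to 0.43 among 9 (nominal 9 × 0.05 = 0.45) and 0.59 to 0.68 among 15 (nominal 0.75).

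**Estimates after selection.**

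- Nominal 95% intervals for retained factors covered the true value in about 49% to 86% of cases. Coverage was worst when no candidate had an effect and best when two had strong effects. Most of the shortfall comes from retained factors with no real effect.
- Where two candidates had a true odds ratio of 1.5 per SD, the median reported odds ratio among those detected was about 2.0 to 2.9.
- Five prespecified factors in a Firth model, with no selection, gave nearly unbiased estimates and 96% to 98% coverage.

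**The case against.** **It is already disclosed.** The Discussion says that predictors are not powered and that the output is preliminary, and a future study would test the hypotheses again. That stands for power and status, and it limits how serious the point is. But a warning about power tells the reader that real predictors may be missed. It does not say that those reported will be too large or that their intervals will under-cover, and the analysis section keeps its significance rule.

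**Selection does not raise the false-positive rate.** This is correct. A reader might set 31% to 51% against 5% and blame the stepwise procedure. But 5% is a per-test level, and the excess is ordinary multiplicity over 9 to 15 candidates. The damage done by selection is in the estimates and intervals.

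**The selected factors need not be mostly chance.** A reader might infer that they would be. That holds only if true effects are absent or very weak. With two real predictors among nine, false factors were about 46% (n=49) or 28% (n=90) of those declared at an odds ratio of 1.5 per SD, and about 20% or 15% at 2. A longer candidate list would raise these shares.

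**The usual-care restriction is deliberate.** The Introduction sets the objective as factors affecting uptake under usual conditions, so the restriction fits. Making all mothers the main analysis would change the question.

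**Events may exceed the estimate.** Eligibility requires willingness to vaccinate, and every mother hears the clinic talk, so uptake could be above 28.5%. This stands as an uncertainty.

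**The Abstract merely condenses.** It does not name an analysis set, so this is a mismatch to tidy rather than a firm contradiction.

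**Conclusion.** The point holds for the estimates. With about 14 to 26 events and at least nine candidates (1.6 to 2.8 events each), the stated procedure will give an unstable choice of factors. Intervals for retained factors will cover well below 95% (about 49% to 86% in simulation), and the odds ratios of detected predictors will be exaggerated (1.5 reported at about 2.0 to 2.9). At least one false factor can be expected in roughly a third to a half of trials if nothing is truly predictive, which is about what unadjusted multiple testing would give.

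The event counts assume 1:1 allocation, 20% attrition and 28.5% uptake. The simulation figures assume independent, normally distributed candidates. Their exact values would move with correlated or categorical variables, but the direction would not. The range of event counts reflects the 123 against 224 discrepancy, which is a separate matter. This is a secondary analysis and the primary result is untouched, so the change is advisable rather than critical.

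**What to change.** In Data management and statistical analysis:

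1. Delete the P<0.10 screen and the backward/AIC selection.
2. Prespecify four or five predictors on subject-matter grounds and keep all of them in one Firth- or ridge-penalised logistic model in the usual-care arm, which matches the stated objective. With five single-parameter predictors this is 14.0/5 = 2.8 to 25.5/5 = 5.1 events per parameter. That is still sparse, hence the penalty.
3. Report odds ratios with 95% intervals, labelled exploratory where the method is described. Remove the P<0.05 rule and the independently-associated wording for this model.
4. Optionally add, as a sensitivity analysis, a model in all randomised mothers with arm as a covariate. It assumes similar predictor effects in both arms. The gain in events depends on the intervention effect. If the effect is 30 points, the totals are 49.2 × (0.285 + 0.585) = 43 or 89.6 × 0.87 = 78. If it is 30% relative (28.5% to 37.05%), they are 49.2 × 0.6555 = 32 or 89.6 × 0.6555 = 59.
5. State the same analysis set in the Abstract as in the analysis section.

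The cost is wording and a routine penalised regression; the article says recruitment had not begun at submission. The real price is that fewer factors are examined, and the sponsor must choose them before seeing the data.
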